#### Safety monitoring and side effects

All study procedures and stimulation parameters will follow the most recent international safety and application guidelines for TMS (Rossi et al., 2021). For each participant, a case report form will be maintained to document session attendance, protocol adherence, and the occurrence of any side effects or adverse events based on predefined criteria. Minor adverse effects (e.g., transient headache) will not necessitate withdrawal from the study, although participants will retain the right to discontinue treatment at any time. In contrast, TMS will be immediately interrupted if a serious adverse event occurs (e.g., an epileptic seizure). After the first and the last stimulation session, participants will also complete the TMSens_Q, a standardized questionnaire designed to record any sensations or adverse effects experienced during or after TMS, in order to systematically monitor tolerability and safety (Giustiniani et al., 2022). In addition to minor side effects, potential longer-lasting effects on visuospatial attention due to PPC stimulation will be monitored with pre- and post-stimulation neurocognitive assessment.

### Outcome measures

In the week prior to the start of treatment, all participants will undergo a baseline assessment consisting of: (1) an independent clinical evaluation conducted by a psychiatrist not involved in the study; (2) self-administered clinical scales; (3) an MRI scan including both structural and functional sequences; and (4) an assessment battery comprising behavioral and neurocognitive tasks designed to evaluate implicit body representation, food-related processing, and broader cognitive functions. The post-treatment assessment will take place in the week immediately following the final TMS session and will include the same components as the baseline assessment. Finally, a follow-up evaluation will be conducted 4 months after the post-treatment assessment, repeating all baseline and post-treatment measures, with the exception of the MRI scan. See Figure 2 for a graphical description of the procedure.

**Figure 2 F2:**
[figure not shown]
Schematic representation of the study protocol. Following baseline assessment, participants will be randomized to active or sham TMS and complete 20 stimulation sessions. Post-treatment and follow-up assessments will replicate baseline measures (with the exception of MRI at follow-up).

#### Clinical evaluation

At all three time points, an independent psychiatrist will conduct a semi-structured interview, systematically addressing expectations and concerns about TMS, anxious and depressive symptoms, daily functioning and quality of life, ruminative and repetitive thoughts, and core eating disorders psychopathology. Additional domains such as obsessive-compulsive symptoms, impulsivity levels, and levels of insight will be explored if clinically relevant. This qualitative assessment will complement standardized scales in evaluating symptom change and treatment acceptability. From this interview, the following outcome measures will be extracted: body weight and BMI, presence or return of menses, and any modification of the psychopharmacological treatment. In addition, the psychiatrist will record changes in eating behaviors (restriction, binge episodes, purging, and excessive compensatory exercise), levels of preoccupation with weight and body image, mood and anxiety severity, and global clinical impression (CGI-S/CGI-I). These measures will provide complementary indicators of treatment response and acceptability alongside standardized scales.

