
The primary outcome of the study will be clinical improvement, assessed quantitatively through changes in BMI and scores on eating disorder psychopathology questionnaires, and qualitatively through the clinical judgment of the psychiatrist. We hypothesize that patients assigned to the active stimulation group will show greater BMI increase and greater reduction in psychopathology compared to the sham group.

Given that the stimulation protocol was specifically designed to target body representation and automatic tendencies toward food, secondary outcomes will focus on these aspects. Changes in body representation will be assessed using both an implicit task, which provides a measure of patients' perceived body boundaries, and an explicit task, in which patients will be asked to select the silhouette that best represents their own body. We hypothesize that, following the stimulation protocol, patients will show a more accurate representation of their body, selecting a silhouette closer to their actual body and demonstrating more precise boundary estimations.

Implicit behavioral tendencies toward food will be assessed using an approach–avoidance task. In a previous study, we observed that patients with AN exhibited a reduced tendency to approach food stimuli (Meregalli et al., 2024). We expect that, following the stimulation protocol, a more natural behavioral tendency will be restored, characterized by faster automatic approach of food stimuli.

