#### Randomization and blinding procedure

Randomization will be implemented using patient codes provided by the coil manufacturer. The randomization procedure relies on the certified double-blind system integrated in the MagVenture MagPro platform for sham-controlled rTMS studies. Each participant will be assigned a unique code, corresponding to a pre-generated allocation to active or sham stimulation, which is entered into the TMS device at the beginning of each session. Participant codes are assigned at enrollment by a study member not involved in outcome assessments. Based on this code, the device automatically recognizes whether the participant receives real or sham stimulation, without revealing the stimulation condition to the operator or the participant. The coil is designed with two indistinguishable sides (active and sham), and the system instructs the operator only on whether the coil is in the correct position or needs to be rotated. Thus, the operator is aware only of coil positioning but remains blind to the actual stimulation condition. The randomization sequence is generated and managed externally to the study team through the device-coded procedure, ensuring full allocation concealment. Both participants and study personnel involved in treatment administration are therefore kept blinded to allocation, ensuring a double-blind design. At the end of the treatment, both participants and the operators who administered the stimulation will be asked to guess whether the participant received active or sham stimulation, as a measure of blinding integrity.

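### After treatment, the psychiatrist who rates clinical change must discuss TMS in the same interview and is named neither among those kept blind nor in the guess check, so patients' beliefs about their arm can reach these ratings

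*Protocol article*

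**What the plan says.** The Introduction defines the primary outcome as clinical improvement, measured by BMI and eating-disorder questionnaires and "qualitatively through the clinical judgment of the psychiatrist".

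The Clinical evaluation section sets out the interview behind that judgment. At T0, T1 and T2, "an independent psychiatrist will conduct a semi-structured interview, systematically addressing expectations and concerns about TMS", together with symptoms, functioning and core eating-disorder psychopathology. From this contact the psychiatrist records changes in eating behaviour, preoccupation with weight and body image, mood and anxiety severity, and CGI-S/CGI-I. The section presents the interview as serving both symptom change and treatment acceptability.

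The Randomization and blinding procedure section states who is blind: "Both participants and study personnel involved in treatment administration are therefore kept blinded to allocation, ensuring a double-blind design". It also states who is tested for blinding: at the end of treatment, "both participants and the operators who administered the stimulation will be asked to guess whether the participant received active or sham stimulation".

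The Introduction and the Outcome measures section describe the psychiatrist as independent and outside the study. The article never describes this person as blinded.

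**The concern.** Independence removes allegiance and access to codes. It does not stop a patient from saying which arm she thinks she had, and a required conversation about TMS after 20 sessions gives her a natural opening. The psychiatrist then makes, or has just made, global and symptom ratings that depend on judgment.

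If patients in the active arm believe more often that they were stimulated, and the rater scores such patients more favourably, the active arm looks better on these ratings without any treatment effect. The abstract says that effect sizes from this trial will guide a confirmatory trial, so a distorted clinician rating would carry forward.

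**Working it through.** The plan gives no figure on this point, so the main check is to set the sections side by side.

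1. **Is the rating part of the primary outcome?** Yes, as its qualitative component (Introduction). CGI-I is not named there as primary; it is one of the records from the same interview.
2. **Are TMS topics and ratings in one contact?** Yes, at all three time points (Clinical evaluation). No order is fixed. At T0 no stimulation has been given, so only T1 and T2 matter.
3. **Is the rater in the stated blind?** Not named. The sentence covers participants and those who administer treatment.
4. **Is the rater in the guess check?** No. Participants and operators only.
5. **Can the rater learn the true allocation?** No route is described. The sequence is held externally in device codes, the operator cannot see the condition, and the person who assigns codes takes no part in outcome assessment.
6. **Can beliefs differ by arm?** The Discussion concedes that scalp sensations or sounds may compromise blinding in sham-controlled TMS.

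Steps 5 and 6 define the mechanism: what can reach the rater is belief, not allocation.

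**Illustrative size.** None of the rating shifts or belief shares below comes from the documents.

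Spurious difference = (rating shift for a patient believed active) × (difference between arms in the share believed active)

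- Low: 0.3 × 0.20 = 0.06 CGI-I points
- Middle: 0.5 × (0.65 − 0.35) = 0.15 points
- High: 1.0 × 0.60 = 0.60 points

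The same calculation can be done in SD units. If a share p guesses correctly in each arm, the difference in share believed active is p − (1 − p) = 2p − 1, so the bias is (2p − 1) × b for a rating shift of b SD. The false-positive rate uses a normal approximation for a simple two-arm comparison (two-sided 0.05, noncentrality = bias / √(2/n)), not the planned mixed model. The arm sizes come from the plan: 28/2 = 14 and 34/2 = 17.

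| p | b (SD) | Bias (SD) | False-positive rate, n = 14 | n = 17 |
|---|---|---|---|---|
| 0.5 | any | 0 | 0.050 | 0.050 |
| 0.7 | 0.5 | 0.4 × 0.5 = 0.20 | 0.083 | 0.090 |
| 0.8 | 0.8 | 0.6 × 0.8 = 0.48 | 0.246 | 0.288 |

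With guessing at chance the bias is zero whatever the rating shift.

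**The case against.** A reader might infer that the rater is unblinded. The article does not support that: it shows no path to the true allocation, and the psychiatrist stands outside the study. Only a belief, possibly wrong, can reach the rater.

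A reader might also infer that the bias would go undetected. That is too strong. The participant guess already shows whether beliefs differ by arm; if they do not, this bias between arms is absent. What the guess cannot show is whether beliefs reached the rater.

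Nor is the whole primary outcome exposed. Measured BMI is largely protected. Questionnaires carry the patient's belief whoever the rater is, so the proposed change does nothing for them. Interview ratings rest partly on what the patient reports, so reordering removes only part of the effect on them. The article itself treats the interview measures as complementary to the standardized scales.

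Three further points have weight. The interview is not said to ask about sensations or allocation, so disclosure is plausible but not certain. The Discussion expects milder discomfort at this site than with frontal stimulation, which tempers the sensory-cue premise. And the article is condensed: rater blinding may be stated in the full protocol, and silence on it alone would not be a finding. What remains is what the article does fix: TMS discussion and subjective ratings in one contact, and two lists that leave the rater out.

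**Conclusion.** The point holds in limited form. At T1 and T2 the plan puts a required discussion of TMS into the interview that produces the clinician ratings, and it names the psychiatrist neither among those kept blind nor among those who guess. Those ratings would be biased between arms if two conditions both hold: beliefs differ by arm, and beliefs shift the rating. The article concedes that the first is possible; the second is an assumption. The size cannot be derived from the documents, and the tenfold span of the illustration (0.06 to 0.60 CGI-I points) shows how little is known. This is an inexpensive weakness to remove, not evidence that the trial is unblinded.

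**What to change.** In the Clinical evaluation section, for T1 and T2:

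- The psychiatrist completes and locks CGI-S/CGI-I, the eating-behaviour, mood and anxiety ratings and the overall clinical judgment before any TMS topic is raised. Alternatively, the TMS expectation and acceptability items move to the Qualtrics battery that patients already complete.
- Patients are asked beforehand not to tell the psychiatrist which arm they think they had.

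In the Randomization and blinding procedure section:

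- Name the psychiatrist among those kept blind.
- Add a psychiatrist guess, recorded after the ratings are locked. It will partly reflect observed improvement, so it should be read alongside the participant guess.

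The cost is a more scripted interview and one extra item, with no added visit or staff. Little acceptability information is lost, because the TMSens_Q and the 0–100 satisfaction scale already collect sensations and satisfaction elsewhere.

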#### Self-administered scales

At all three time points, patients will complete the following self-administered scales using the online platform Qualtrics: (1) the *Eating Disorder Examination Questionnaire* (Fairburn and Beglin, 1994), a 28-item measure assessing the severity of eating disorder psychopathology across the domains of restraint, eating concern, weight concern, and shape concern; (2) the *State-Trait Anxiety Inventory* (Spielberger, 1983), a 40-item questionnaire that assesses both state and trait anxiety symptoms; (3) the *Depression Anxiety Stress Scales* (Lovibond and Lovibond, 1996), a 21-item instrument assessing symptoms of depression, anxiety, and stress; (4) the *Multidimensional Assessment of Interoceptive Awareness* (Mehling et al., 2012), a 32-item scale evaluating multiple facets of interoceptive body awareness (e.g., noticing, attention regulation, and emotional awareness; 5) the *UPPS-P Impulsive Behavior Scale* (Whiteside and Lynam, 2012), which measures five distinct dimensions of impulsivity: negative urgency, lack of premeditation, lack of perseverance, sensation seeking, and positive urgency; the (6) *Body Shape Questionnaire* (Cooper et al., 1987), a 34-item questionnaire developed to evaluate negative self-appraisal of body shape (e.g., the desire to lose weight, fear of gaining weight, and self-devaluation in relation to physical appearance); and (7) the *Weight Bias Internalization Scale* (Pearl and Puhl, 2014), an 11-item questionnaire developed to measure the degree of negative beliefs about one's weight or body size.

#### MRI protocol

Structural MRI data will be acquired on a 3T Philips Ingenia scanner (TR = 6.8 ms, TE = 3.1 ms, slice thickness = 1 mm, Flip Angle = 8°, 181 × 480 × 480 matrix, voxel size = 1 × 1 × 1 mm^3^). Preprocessing of the structural images will involve brain extraction and bias field correction by means of ANTs (Advanced Normalization Tools; antBrainExtraction and N4BiasFieldCorrection functions; Tustison et al., 2021). The FMRIB Software Library (FSL) FMRIB's Automated Segmentation Tool (FAST) algorithm will be used to perform tissue segmentation (Zhang et al., 2001), followed by MNI normalization by means of ANTs (Tustison et al., 2021). Functional MRI data will be acquired on a 3T Philips Ingenia scanner (TR = 800 ms, TE = 24.6 ms, flip angle = 60°, number of volumes = 800, voxel size = 2.78 × 2.78 × 3 mm, 96 × 96 × 56 matrix). Preprocessing of the functional images will involve motion correction by means of mcflirt (Jenkinson et al., 2002), followed by bias field correction by means of ANTS (Tustison et al., 2021). FMRIB's Linear Image Registration Tool (FLIRT) will be used to coregister each participant's functional and anatomical volume using 12 degrees of freedom and a boundary-based constriction relying on each individual white matter mask (Greve and Fischl, 2009). CompCor (Components based Noise Correction; Behzadi et al., 2007) and ART (Artifact Rejection Toolbox) functions will be further applied to perform scrubbing and remove additional noise components following the CONN functional connectivity toolbox (MATLAB-based) (CONN) denoising pipelines (Nieto-Castanon, 2020). A gaussian smoothing kernel with a full width at half maximum of 6 mm will be applied as a last step to further improve the signal to noise ratio. Finally, the Schaefer 200 functional parcellation (Schaefer et al., 2018) will be coregistered to the individual EPI space by applying the transformation matrix of the MNI to structural-functional coregistration. The same procedure will be applied to bring the networks' overlap map from its MNI space to the individual space. Functional timeseries will then be extracted from both the atlas and the networks' overlap map, representing the fluctuations of the BOLD signal across all volumes of the acquisition (*n* = 800).

The same acquisition and preprocessing steps will be repeated for the post-treatment acquisition.

#### Behavioral and neurocognitive tasks

At all time-points participants will undergo an assessment battery including the following behavioral and neurocognitive tasks:

(1) *Virtual reality task to assess implicit body representation*. In this task, participants see in virtual reality a green dot approaching them from different orientations and at varying heights. They are instructed to press a button at the exact moment they perceive the stimulus to have “touched” their body. This procedure allows for the construction of a perceptual map of body boundaries in the absence of direct visual or tactile feedback, thereby providing an implicit measure of body size distortion.(2) *Figure rating scale*. Participants will be presented with a series of computer-generated silhouettes created using the MakeHuman software, representing a range of BMI from 12 to 38. They will be asked to select the silhouette that best corresponds to their perceived current body shape and the silhouette that represents their desired body shape. Two derived indices will be calculated: the difference between perceived BMI and actual BMI, providing an implicit measure of body size distortion, and the difference between desired BMI and perceived BMI, serving as an index of body dissatisfaction.(3) *Peripersonal space task in the presence of food stimuli*. This task is an adaptation from an established paradigm for measuring peripersonal space (PPS; Serino, 2019). As in standard PPS tasks, participants are immersed in virtual reality and presented with visual stimuli approaching them. Simultaneously, a tactile stimulus is delivered to the participant, who is instructed to respond as quickly as possible by pressing a response button. The tactile stimulus is administered when the visual stimulus is at one of five possible distances from the participant. The underlying principle is that when the visual stimulus enters the PPS, the response to the tactile stimulus is facilitated, allowing reaction times to serve as an implicit measure of PPS extent. Given that PPS representation is known to be modulated by various factors, including the nature of the approaching stimulus, we will assess both the extent and shape of PPS in the presence of high-calorie food stimuli and neutral objects.(4) *Approach-avoidance task toward food stimuli*. Implicit behavioral tendencies toward food stimuli will be assessed using a mobile version of the approach-avoidance task (Collantoni et al., 2023). In this task, participants are instructed to either approach images by pulling their phone toward themselves or avoid images by pushing it away. Stimuli include high-calorie foods, low-calorie foods, and neutral objects. Reaction times for each movement will be recorded, and an approach bias score will be calculated by subtracting avoidance reaction times from approach reaction times, providing an index of implicit motivational tendencies toward the different types of stimuli.(5) *Heartbeat counting task*. Interoceptive accuracy will be assessed using the heartbeat counting task (Garfinkel et al., 2015). Participants are asked to silently count their own heartbeats over several fixed time intervals (e.g., 25, 35, 45 s) without manually checking their pulse. The counted heartbeats are then compared to the actual number of heartbeats recorded via a heart rate monitor, allowing calculation of an accuracy score that reflects the participant's ability to perceive internal bodily signals.(6) *Trail making test*. The TMT (Reitan, 1958) will be used to assess cognitive flexibility. The task consists of two parts: Part A, in which participants connect numbered circles in ascending order as quickly as possible, primarily measuring processing speed; and Part B, in which participants alternate between numbers and letters in ascending/alphabetical order (1-A-2-B, etc.), requiring set-shifting and cognitive flexibility. The time to complete each part is recorded, and the difference or ratio between Part B and Part A is commonly used as a proxy of executive functioning and mental flexibility.(7) *Rey-Osterrieth complex figure*. The ROCF (Osterrieth, 1944) will be administered to evaluate visuospatial abilities, with a specific focus on assessing central coherence during figure construction. The test consists in the copy of a complex geometric figure, followed by a recall trial of the same figure after a 3-min interval filled with non-interference tasks. The entire procedure will be video-recorded and conducted using the pen switching method. Scoring will be performed according to the Taylor method for *Accuracy* and Booth's criteria for the *Central Coherence Index* (Lezak et al., 2004). To minimize implicit learning that may occur with repeated administration of the same figure in longitudinal assessments, the Modified Taylor Complex Figure (MTCF), an equivalent form of the ROCF, will be used interchangeably in the pre-post treatment evaluation (Hubley and Jassal, 2006). Scoring of the MTCF will be conducted using the same standardized methods as for the ROCF, appropriately adapted.

The order of task presentation will be randomized across participants and sessions. Each assessment session is expected to last approximately 1.5 h.

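### The approach bias score runs opposite to its name with no reading direction given, and the silhouette index is a plain difference although the hypothesis is about accuracy

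*Protocol article*

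**What the plan says.** Body representation and automatic tendencies toward food are the domains of the secondary outcomes: "secondary outcomes will focus on these aspects" (Introduction).

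**Approach–avoidance task.** The Introduction cites the trial team's own published study, in which "patients with AN exhibited a reduced tendency to approach food stimuli", and expects a more natural tendency after stimulation, "characterized by faster automatic approach of food stimuli". Item (4) of Behavioral and neurocognitive tasks fixes the score: "an approach bias score will be calculated by subtracting avoidance reaction times from approach reaction times". It describes the result only as "providing an index of implicit motivational tendencies toward the different types of stimuli".

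**Figure rating scale.** The Introduction expects a more accurate body representation, with patients "selecting a silhouette closer to their actual body". Item (2) of Behavioral and neurocognitive tasks derives two indices. One is "the difference between perceived BMI and actual BMI, providing an implicit measure of body size distortion". The other is "the difference between desired BMI and perceived BMI, serving as an index of body dissatisfaction". Neither is stated as an absolute value.

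**Analysis.** The section on clinical, behavioral and cognitive outcomes applies one model to every outcome: a linear mixed model with group, time and their interaction, and a random intercept per participant. It reports effect sizes, 95% confidence intervals and p-values, and specifies no directional test.

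**The concern.** These are two definitions that the article itself fixes, set against hypotheses that it also states. They are therefore not details left open for a fuller plan.

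The first is a matter of labelling. A reader who meets a negative group-by-time estimate on a score called approach bias will naturally take it to mean less approach. Under the stated formula it means relatively faster approach. The same reader would expect patients with a weak approach tendency to score low, whereas they score high.

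The second is a matter of measurement. Closeness to the true body is a distance from zero, and a plain difference is not a distance. Over- and under-estimation offset each other in the group mean, and a patient who passes from one side of the truth to the other registers a large shift whatever happens to her accuracy. The secondary hypothesis on explicit body representation could then be judged on a quantity that does not express it.

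**Working it through.** The documents give no reaction times and no silhouette errors, so there is no stated figure to reproduce. All values below are assumptions chosen to show how the definitions behave.

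**1. Direction of the approach score.** Stated formula: score = approach RT − avoidance RT. Hold avoidance RT at 650 ms.

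- Approach 700 ms: 700 − 650 = +50; reversed formula −50.
- Approach 650 ms: 650 − 650 = 0; reversed formula 0.
- Approach 600 ms: 600 − 650 = −50; reversed formula +50.

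With avoidance fixed, each millisecond of faster approach lowers the stated score by one millisecond. The hypothesised benefit appears as a fall.

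**2. Effect on inference.** One data set was simulated with 34 participants, three time points, a between-participant SD of 50 ms, a residual SD of 50 ms and an active-arm shift of −60 ms after baseline. The planned type of model was fitted to the score and to its negative.

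- Stated score: interaction estimates −29.8 and −53.8, p = 0.149 and 0.009.
- Negated score: interaction estimates +29.8 and +53.8, p = 0.149 and 0.009.

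Only the sign changes.

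**3. Silhouette index, mixed errors.** Index d = perceived BMI − actual BMI. Suppose four patients in an arm start at +4, +4, −4, −4 and every error halves.

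- Signed mean before: (4 + 4 − 4 − 4)/4 = 0. After: (2 + 2 − 2 − 2)/4 = 0. Change 0.
- Absolute mean before: 4. After: 2. Change −2.

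If the comparison arm starts the same and does not change, the group-by-time contrast is 0 − 0 = 0 on the signed index and −2 − 0 = −2 on the absolute index. The gain in accuracy is invisible to the first and visible to the second.

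**4. Silhouette index, overshoot.** One patient moves from +2 to −3. The signed change is −3 − 2 = −5, which looks like a large reduction in over-estimation. The absolute change is 3 − 2 = +1, a loss of accuracy.

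**5. When the two agree.** If all four patients start at +4 and end at +2, both indices change by −2. If all start at −4 and end at −2, the signed index changes by +2 and the absolute by −2: the same size, with the sign explained by direction. Agreement needs a common direction of error and no overshoot.

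**The case against.** **On the approach score.** A reader might infer that a real benefit would be recorded as harm. The documents do not support that. They never say that a higher score is better, the hypothesis is given in terms of raw speed, and no directional test is planned. Anyone who applies the formula with care can work out that a fall is predicted, and step 2 shows that inference is unaffected. This objection stands, and it limits the point to a mismatch between name and formula with no stated reading.

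**On neutral objects.** A reader might also infer that food scores will be analysed without reference to neutral stimuli, so that a general change in pull or push speed passes for a food effect. The article does not say this. The task includes neutral objects, the score is described for the different stimulus types, and the contrast between types can properly be left to a fuller plan. A difference of differences would also be noisier. That inference is not part of this point.

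**On the silhouette index.** The strongest reply is that the article never uses the word signed, that direction is informative about distortion, that cancellation needs a mixture of over- and under-estimators which the documents do not describe, and that a virtual reality task also measures body representation. Much of this is fair. But a plain difference is what is written, it is one of only two indices derived from the task, and neither expresses the accuracy that the hypothesis names. The virtual reality task addresses implicit boundaries and does not repair the silhouette measure.

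**Conclusion.** The point holds in two separate parts of unequal weight.

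The approach bias score runs against its name and comes without a reading direction. The risk is misinterpretation of a secondary outcome; the size of the effect, its confidence interval apart from sign, and its p-value are untouched.

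The silhouette index does not match its hypothesis, and this can alter a result. It can miss a gain in accuracy altogether (signed change 0 against absolute change −2 in step 3) or show a shift towards apparent improvement when accuracy worsens (−5 against +1 in step 4). How much this matters in the trial depends on the mix of over- and under-estimators and on how often patients overshoot, which the documents do not give. If all err the same way and none overshoots, the two indices lead to the same conclusion.

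**What to change.** In item (4) of Behavioral and neurocognitive tasks, either define the score as avoidance RT minus approach RT, so that higher means more approach, or keep the formula and state that lower values mean stronger approach. In either case give the expected sign of the change for food stimuli. This costs one sentence.

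In item (2), state that the accuracy hypothesis is tested on |perceived BMI − actual BMI|, and keep the signed difference as a measure of direction. No new data are needed. The cost is one more analysis and a score bounded at zero that is likely to be skewed, so the residuals of the mixed model need checking.

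Both definitions should be settled before unblinding, so that neither the direction nor the metric is chosen with the results in view.
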